### Data Collection and Measures

#### VR

VR technology encompasses computer technology enabled by, in this case, head-mounted displays (goggles) in which one experiences and physically moves around in scenarios that closely represent real life. Participants will be fully immersed in the virtual environment, providing visual and auditory stimuli to create illusive feelings of physically existing in that environment [64]. VR technology is an innovative and successful strategy for training and research on health and safety behavior among both adults [64,65] and children, with a large body of child research focused on street-crossing [54,55,66,67] and bicycling tasks [68,69]. In this study, we use VR technology (HTC Vive Pro Eye VR headset), with 4 SteamVR 2.0 Base Stations defining a VR area of 6 × 7 m for free movement, to test how children manage different kinds of risk situations.

On the basis of research into common causes of injury among children [1-3], we developed three categories of VR risk scenarios: (1) street crossing, (2) crossing a river, and (3) Balancing on high playground equipment. All scenarios include various tasks with increasing levels of difficulty and risk.

The VR scenarios were developed through collaboration between the research group and a VR design company (Nordic Neurotech AS) from September 2021 to March 2022. The aim was to create fully immersive scenarios in a virtual world where children performed risky tasks and judged the experience to be as similar to reality as possible. The veracity of the VR scenarios is strengthened through realistic sounds integrated in the VR goggle headphones (eg, city sounds, car sounds, birdsongs, and sounds of running water). In all VR scenarios, children receive the same prerecorded messages before each task, telling them what to do (eg, “Cross the river without falling down”).

The VR software provides data output in the form of a text file (.txt), with one line for each recorded hertz. Within each line, the position of the headset and the 5 Vive trackers are provided using the x, y, and z coordinates. Data on the headset and tracker’s rotation are also available in the data set. Similarly, the position of every simulated moving object (cars and bicycles) is represented with coordinates. Quantitative data from this text file are obtained through MATLAB analysis.

##### Street Crossing

The street crossing scenario consists of 2 urban traffic environments. In both environments, children are exposed to 3 different tasks with varying levels of risk, with risk level varied by manipulating harm severity and probability of being hit [70,71]. The lowest risk scenario involves bicycles and the highest involves both cars and bicycles. Probability risk is adjusted through traffic density and speed and by including traffic from 1 direction versus 2 directions. The first environment represents a bicycle pathway and includes buildings, trees, and grass surfaces (Figure 1, left side). The second environment replicates a busy urban street with buildings, sidewalks, and parked cars (Figure 1, right side); it includes a cars-only task as well as tasks with both cars and bicycles. In all cases, the child’s goal is to cross the path or street without getting struck by a car or bicycle. All street-crossing scenarios incorporate realistic sounds from the urban environment (the sound of cars, bikes, people, etc).

If the child is hit by a bike or car, a new trial on that same task is provided. If the child is hit a second time, the VR continues to the next task. The time to complete tasks in the street-crossing scenario will vary across children because they will be free to take the time they need, both to assess the situation before acting and to perform the crossing. Pilot research found that children spent on average 3 minutes to complete the street-crossing tasks (Figure 1, left and right side).

Quantitative data points that will be obtained from the street-crossing tasks include measures related to the child’s risk assessment (eg, time used to assess the environment before crossing the street and fixation on vehicles before crossing the street), risk willingness (eg, distance to vehicles when starting to cross the street), risk handling (eg, speed of crossing, running, acceleration, and deceleration), and risk management outcomes (eg, number of times the child was hit or almost hit by vehicles).

**Figure 1 figure1:**
[figure not shown]
Screenshots of the virtual bicycle pathway environment and the virtual street environment. The red square represents the point where children are asked to move to.

##### River Crossing

The river-crossing scenario presents a rural environment with a flowing river. Children complete 7 tasks, each with the goal of crossing the river without falling into the water. Five of the tasks involve balancing on planks to cross the river, whereas in the other 2 tasks children must step or jump between elevated stones to cross. Similar to the street-crossing scenario, the 7 river-crossing tasks vary in risk, based on harm severity and probability of failure [70,71]. Harm severity risk levels are manipulated by the speed and depth of the river and the presence of rocks in the water. Probability risk is adjusted by the width (between 8 and 38 cm) of the balance planks and the placement of stepping stones (ie, how close or far they are from each other). In all river-crossing scenarios, children hear sounds from a rural nature environment (eg, the sound of running water, wind, and birds).

If the child falls into the water, a new trial on that same task is provided. If the child falls a second time, the VR continues to the next task. The time required to complete the river-crossing scenario tasks will vary between children because they are free to take the time they need, both to assess the situation before acting and to perform the crossing. Pilot research found that children spent on average 3 minutes to complete the river-crossing tasks (Figure 2).

Quantitative data points that will be obtained in the river-crossing tasks include measures related to the child’s risk assessment (eg, time used to assess the environment before crossing the river), risk willingness (eg, opting out of the task, jumping between rocks, and choosing the narrow plank), risk handling (eg, speed of crossing, keeping both feet on the ground while balancing, acceleration, and deceleration), and risk management outcomes (eg, number of times the child falls into the river).

**Figure 2 figure2:**
[figure not shown]
Screenshots of the river crossing scenario, one of the plank tasks and one of the stepping stones task.

##### Playground

The playground scenario presents a balancing play structure in an urban playground environment. Unlike the first 2 scenarios, where children perceive a fixed and objective task to cross the street or river, in the playground scenario, children are free to move and play as they like, without fixed objectives or goals. The virtual balancing structure comprises a complex pattern of balance beams of varying widths, vertical pillars of varying diameters, and 4 different height zones above the ground surface. Similar to the first 2 scenarios, variation in harm severity and probability of failure occur within the playground scenario. Probability risk varies by the difficulty of the play areas (ie, a child could choose to balance on the narrowest beams or jump out to one of the pillars), whereas harm severity varies by the height zones children choose to explore. In the study, children are provided 3 minutes to explore the playground before the scenario automatically ends. If a child falls off the playground equipment, he or she will enter the starting point of the playground task and have the opportunity to further play and explore during the remaining time in the 3-minute period. The sounds of an urban environment (eg, cars, bikes, or people) are emitted through the headphones (Figure 3).

**Figure 3 figure3:**
[figure not shown]
Screen shot of the playground scenario.

Quantitative data points that will be obtained during the playground task include measures related to the child’s risk assessment (eg, time used before starting to balance on a beam), risk willingness (eg, stepping out on pillars, jumping over gaps, and time spent in high-risk zones), risk handling (eg, speed of balancing, keeping both feet on the ground while balancing, acceleration, or deceleration), and risk management outcomes (eg, number of times the child falls off the playground equipment).

#### Eye Tracking

Eye-tracking technology is used extensively in research to explore topics such as how humans learn [72] and how humans use their gaze when performing safety practices [73], as well as for medical training (eg, in laparoscopic surgery or when detecting anatomical injuries) [74]. The technology is also used to measure how children’s eye movements are related to their performance, risk, and safety behavior when cycling [69]. In street-crossing VR tasks, eye-tracking data from one study demonstrated that children’s ability to focus on factors most salient for a safe crossing is compromised when the environment is more visually loaded, possibly causing them to miss critical information [75]. However, knowledge about the relationships between children’s eye movements and their risk management is limited.

In this study, we will use eye-tracking technology (Tobii Pro) integrated in the VR goggles to explore how children use their gaze and eye movements to identify risk factors that guide their navigation, bodily movement, and risk decisions in the VR scenario environments. Eye-tracking data will be logged in 90 Hz and provide data on the eye-tracking target (x, y, and z coordinates), including what object the child looks at. Because this information is provided continuously with a refresh rate of 90 Hz, it can be transformed into variables describing the length of time children look at various objects or parts of the environment, direction, and shifts of the child’s focus and information about how children follow moving objects such as vehicles with their eyes (Figure 4).

**Figure 4 figure4:**
[figure not shown]
Screen shot from the bicycle path scenario, showing eye-tracking as a blue line.

The eye-tracking data from all VR tasks will be processed in MATLAB to generate quantitative measures related to the child’s risk assessment (eg, fixation on vehicles before crossing the street, looking at oncoming or departing bicycles and cars before crossing, looking both ways before crossing the street, looking at planks and balance beams before and while crossing, looking at water and rocks, and looking at the ground below the playground equipment) and risk handling (eg, looking at oncoming bicycles and cars while crossing).

#### Motion Capturing and Analysis

Part of the innovative approach of this project is assessing children’s motor competence when they navigate and explore VR scenarios. We will accomplish this through whole-body motion capture, which offers a comprehensive understanding of the individual’s qualitative and quantitative signatures of movement. This methodology represents a novel approach toward the assessment and understanding of motor competence in children, extending current and predominant approaches that focus on tasks with down-scaled complexity, detailed instructions, and highly specific assessment criteria. Existing approaches have been critiqued for their lack of developmental and ecological validity [76].

The Xsens MTw Awinda system of motion-capturing technology is an innovative and user-friendly method to track human motion in real time. The portable system provides accurate time-synchronized data with accurate measures of whole-body movements. It has been used widely in research to capture human motion in sport, physical activity, and rehabilitation [77-80]. In this project, MTw Awinda is used to track and capture children’s motion and bodily movements when handling risk in VR scenarios.

The Xsens MTw Awinda system consists of 17 wireless inertial measurement units, each of which consists of a gyroscope, an accelerometer, and a magnetometer. MTw Awinda samples data at 60 Hz through a proprietary radio protocol at 2.4 GHz, which provides accurate time synchronization across the wireless network within 10 µs. Physically, the inertial measurement units are 47 × 30 × 13 mm, weigh 16 g, and are attached to the children with Velcro straps on the following anatomical locations: forehead, sternum, palmar side of the hand (right or left), lateral side of the upper arm (right or left), wrist (right or left), lateral side of the lower leg (right or left), lateral thigh (right or left), foot (right or left), upper part of the scapula (right or left), and lower back (L5, height of the iliac spine). The system provides 3D kinematical data (position, velocity, acceleration, and orientation) on the movement of 23 different segments (eg, head, upper hand, or foot) as well as angular movements of 22 different joints. The dynamic accuracy is 0.75° root-mean-square (RMS) and 1.5° RMS for roll or pitch and heading, respectively. In the ViRMa project, children will wear the Xsens MTw Awinda sensors while completing all VR tasks.

The raw Xsens data will be exported and further processed in MATLAB R2022a (MathWorks Inc) by algorithms developed by the research group. After inspection of the frequency spectrum content of the raw data with the periodogram method, low-pass (zero-phase) Butterworth filtering procedures will be applied to remove unwarranted noise. To obtain numeric measures related to children’s motor competence and risk handling strategies (ie, bodily movement strategies), 2 main approaches to movement analysis will be applied. First, analysis of children’s overall locomotory strategies, defined as the movement (transport) of the entire body as children navigate the VR scenarios, will be conducted by examining the 3D kinematic variability of the pelvis segment (ie, the location of the body center of mass). This analysis generates variables on various motoric risk handling strategies, such as velocity and acceleration profiles (ie, speeding up or slowing down), angle of projection when moving across the road, and degree or pattern of postural movements to maintain balance and stability. In the second approach, the kinematic variability of the major joints from the whole body (ie, neck, shoulders, elbow, hip, knee, and ankle) will be analyzed. Here, numeric measures closely associated with motor competence, such as degree of repetitiveness and variation in joint movements (entropy), association between upper body versus lower body movements, and interjoint coordination patterns, will be examined.

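### The pelvis segment is equated with the body's centre of mass for balance variables as well as transport, so balancing with the trunk or arms may be misread or missed

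*Protocol article*

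**What the plan says.** All of this is in the protocol article.

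- **First approach (Motion Capturing and Analysis).** It is introduced as "analysis of children’s overall locomotory strategies, defined as the movement (transport) of the entire body as children navigate the VR scenarios" and is carried out by "examining the 3D kinematic variability of the pelvis segment (ie, the location of the body center of mass"). Its outputs are described as motor strategies for handling risk. They include speed and acceleration profiles, the angle of crossing, and the "degree or pattern of postural movements to maintain balance and stability".
- **Second approach (same section).** Here "the kinematic variability of the major joints from the whole body (ie, neck, shoulders, elbow, hip, knee, and ankle) will be analyzed". It serves measures tied to motor competence, such as entropy of joint movements; in addition, "association between upper body versus lower body movements, and interjoint coordination patterns, will be examined".
- **Data available (same section).** The system gives "3D kinematical data (position, velocity, acceleration, and orientation) on the movement of 23 different segments".
- **Balance tasks (River Crossing, Playground).** Five of the seven river tasks are plank crossings, with difficulty set partly by "the width (between 8 and 38 cm) of the balance planks". The playground is a structure of beams and pillars.
- **Use of the variables (Analysis).** Movement profiles are clustered from the motion-capture data. Global measures, including risk handling, are built by exploratory factor analysis from the VR, eye-tracking and motion-capture data.

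**The concern.** The parenthesis in the first approach states an identity, not an approximation. For transport this does little harm: over a crossing, pelvis and centre of mass travel together. For balancing, the distance between the two is part of what the child controls. A child may swing the hips one way and the trunk the other and keep the centre of mass almost still. Another may hold the hips still and correct with the trunk or arms. A variable based on the pelvis alone describes neither correctly if it is read as movement of the centre of mass.

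This matters because one of the two aims of this stage is to establish valid measures of risk management and its parts, and balance is central to two of the three scenarios. A mislabelled balance variable could enter the risk-handling factor and the movement clusters.

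**Working it through.** The article gives no figure on this point, so there is nothing to reproduce. The sizes below rest on assumed body proportions.

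**1. Model.** Let p be the sideways position of the pelvis, d the displacement of the upper body's own centre relative to the pelvis, and f the upper body's share of body mass. Relative to upright posture, the whole-body centre of mass is

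c = p + f × d.

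The gap between centre of mass and pelvis is therefore f × d.

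**2. Size for a trunk lean.** With a lean of angle θ, d = 0.20 × height × sin θ. Assumptions: height 1.20 to 1.40 m, f = 0.55 to 0.65, and the upper-body centre 0.20 of height above the hips.

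| Lean | Low end | High end |
|---|---|---|
| 10° (sin = 0.174) | 0.24 m × 0.174 × 0.55 = 2.3 cm | 0.28 m × 0.174 × 0.65 = 3.2 cm |
| 20° (sin = 0.342) | 0.24 m × 0.342 × 0.55 = 4.5 cm | 0.28 m × 0.342 × 0.65 = 6.2 cm |

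**3. Same formula, other assumptions.**
- Upper body, f = 0.4 to 0.6 and d = 5 to 15 cm: 0.4 × 5 = 2.0 cm up to 0.6 × 15 = 9.0 cm.
- Both arms only, f = 0.06 to 0.12 and d = 10 to 30 cm: 0.06 × 10 = 0.6 cm up to 0.12 × 30 = 3.6 cm.

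**4. Scale.** The narrowest virtual plank is 8 cm wide and the widest 38 cm, so half-widths run from 4 to 19 cm. The trunk-lean gap can reach or exceed the smallest half-width; the arms-only gap stays below it. This comparison gives a sense of scale only (see the objection).

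**5. Effect on variability.** The plan analyses variability, so what counts is how the gap changes over time. From step 1,

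Var(c) − Var(p) = f² Var(d) + 2f Cov(p, d).

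- Exact counter-movement, p = −f × d: Var(c) = 0 while the pelvis moves through f × d. The pelvis overstates movement of the centre of mass.
- Still pelvis, Var(p) = 0: Var(c) = f² Var(d). The pelvis shows nothing while the centre of mass moves.
- A lean held constant: Var(d) = 0, so the gap adds no variability.

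The error can take either sign, depending on the child's strategy.

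**6. Does the second approach fill the gap?** It records neck, shoulder, elbow and hip movement and relates upper to lower body, so upper-body strategies leave a trace in the data. It is described as serving motor competence, not the balance variables, and joint variability alone does not locate the centre of mass.

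**The case against.** A reader might infer that a child who balances with the trunk or arms will be scored as unstable, and that the ranking of children on handling is reversed. The article does not support this. It defines no stability score and does not say that more movement is worse. The outputs are called strategies, and a hip counter-movement is itself a postural movement made to keep balance. Factor analysis fixes no sign in advance. Step 5 shows that the error can also make a child look steadier. Falls are counted directly in the river and playground tasks, so success at balancing does not depend on the pelvis variable.

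A reader might also take the 4 cm half-plank as the base of support. It is not. Under Strengths and Limitations the authors say that real planks were not possible in this mobile set-up, so children walk on the floor. No part of the article judges balance by the centre of mass over the plank. In addition, 8 cm is the extreme of the range, and every body proportion used above is an assumption.

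Finally, the variable is one example among many candidates, the factor items are screened on loadings and R², and a condensed article need not spell out its algorithms.

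All of this limits the consequence. It does not remove the stated identity or the fact that balance variables are drawn from it. That choice is written in the article, not left open.

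**Conclusion.** The point holds as one of measurement validity, of modest weight in an exploratory study. The article equates the pelvis with the centre of mass and uses it for balance as well as transport. For transport this is acceptable. For balance, a trunk lean of 10 to 20 degrees separates the two by about 2 to 6 cm under the proportions assumed above, and the second set of assumptions gives 2 to 9 cm for the upper body. Upper-body balance strategies may then be misread or missed. The direction is not fixed, the joint-based analysis offsets the loss only in part, and no misclassification of children or reversed ranking is shown. Sample size and significance level are unaffected.

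**What to change.** 1. Reword the parenthesis so that the pelvis is described as a proxy for the centre of mass, and keep it for velocity, acceleration and direction.
2. For the balance and stability variables, compute the whole-body centre of mass as the mass-weighted mean of the 23 segment positions, and use its motion relative to the pelvis or feet.
3. Report how well this measure agrees with the pelvis-based one in the plank, stone and beam tasks.
4. Optionally, express it relative to the virtual plank or beam line, but only where the motion-capture and VR coordinates can be aligned. The article describes no such alignment.

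Cost: extra processing code and a table of segment mass shares, with no new data. Downside: mass shares for children are approximate, so repeat the calculation with a second plausible set and report whether the balance variables change.

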### Child Questionnaires

#### Children’s Sensation Seeking

Sensation-seeking personality, defined as an innate willingness to take risks and the extent to which children seek risk in their everyday life, will be assessed using the Sensation Seeking Scale for Young Children (SSSYC) [81]. A 27-item instrument, the SSSYC was developed to assess sensation seeking among children aged 7-12 years. Each item presents 2 statements of preferences that child respondents choose between. As an example, children are presented the following options: (1) *I am the sort of person who would like to sled fast down a steep hill* compared with (2) *sledding fast down a steep hill sounds scary to me*. The SSSYC includes three subscales, each with strong evidence for internal reliability: (1) thrill seeking (α=.85), (2) behavioral inhibition (α=.83), and (3) behavioral intensity (α=.83) [81]. Selecting the statement indicating higher levels of the measured subscale earns 1 point on the overall subscale score. In the above example, selecting the first option earns 1 point on the thrill-seeking scale, whereas choosing statement 2 earns 0 points.

For this study, the SSSYC was first translated from English to Norwegian by author [name]. Then all primary researchers in the project group discussed the translation to revise unclear wordings and adapt words and phrases to fit the Norwegian context. Next, the Norwegian version of the scale was back-translated to English by a professional translator, and then the 3 versions (original English, translated Norwegian, and back-translated English) were discussed among the project group to ensure that the original meaning of the statements was reflected in addition to being relevant and understandable for Norwegian children. In the ViRMa project, we will administer the SSSYC orally, with a researcher recording the child’s responses on the web.

